# Effectiveness of m-health-based core strengthening exercise and health education for public safety workers with chronic non-specific low back pain: study protocol for a superiority randomized controlled trial (SAFEBACK)

**DOI:** 10.1186/s13063-023-07833-9

**Published:** 2023-12-01

**Keywords:** Low back pain, Mobile health, Physical exercise

## Abstract

**Background:**

Low back pain (LBP) is the leading cause of years lived with disability worldwide. Public safety workers are highly exposed to physically demanding activities and inappropriate postures, increasing the risk of experiencing LBP. Smartphone app-based self-managed interventions may be an alternative for chronic non-specific LBP (CNSLBP) treatment. This study aims to evaluate the effectiveness of a smartphone app-based self-managed exercise program plus health education, compared to a health education program alone, on neuromuscular and perceptual outcomes in police officers and firefighters with CNSLBP.

**Methods:**

This is a parallel, two-armed, blinded evaluator randomized clinical trial. Police officers and firefighters (from public safety institutions in the Rio Grande do Sul state, Brazil) will be randomly assigned to a m-health self-managed exercise program (twice a week) plus health education or health education alone. Self-management exercise program components are mobility and core resistance exercises, available on the app. Follow-ups will be conducted post-treatment (8 weeks) and 16 weeks after randomization. The co-primary outcomes will be pain intensity and disability post-treatment (8 weeks). Secondary outcomes will be biopsychosocial factors related to CNSLBP.

**Discussion:**

We hypothesize that the effects of a smartphone app-based self-managed exercise program on co-primary and secondary outcomes will be superior, compared to the health education only in public safety workers with CNSLBP.

**Trial registration:**

The study was prospectively registered at ClinicalTrials.gov (NCT05481996. Registered on August 01, 2022).

**Supplementary Information:**

The online version contains supplementary material available at 10.1186/s13063-023-07833-9.

## Background

Low back pain (LBP) is the leading cause of years lived with disability [1, 2], resulting in high rates of productivity loss worldwide [2]. One out of four adults experience chronic LBP [3] (CLBP; pain persisting for more than 12 weeks) [4] worldwide. This prevalence is 2.5 times higher in working populations [5]. The CLBP prevalence in public safety workers (e.g., police officers and firefighters) ranges from 28.7 to 76.2% [6–8], and in Brazil, LBP is the main reason for sick leave in this population [9–11].

Several factors can increase the risk of experiencing LBP, including physical (e.g., regular lifting), psychological (e.g., depression), and poor general health (e.g., sleep problems) [12]. Notably, the daily activities of police officers and firefighters inherently involve these factors. These professionals often adopt poor postures, such as prolonged standing while fighting fires or while patrolling in police cars [13], frequently engage in heavy lifting (e.g., carrying body armor, weapons, tools, and oxygen cylinders) [14, 15], experience mentally stressful situations (e.g., armed confrontations and accidents with fatalities) [13, 16, 17], and face challenges affecting their sleep quality (e.g., long work shifts) [18, 19].

The association between subjective (i.e., pain) and objective measures (i.e., endurance and strength of the trunk muscles) in individuals with CLBP [20] plays a crucial role in the understanding and management of CLBP among public safety workers (i.e., police officers and firefighters). Current evidence supports the effectiveness of interventions involving physical exercises, particularly core strengthening, in comparison to usual treatments for reducing pain and improving functional disability in CLBP patients [21, 22]. In addition, internet-based self-management programs (e.g., websites, video conferencing, smartphone apps) have gained widespread recognition for CLBP rehabilitation [23–25]. Telerehabilitation, specifically using a mobile-based (m-health) exercise program, helps overcome several potential barriers to access traditional in-person healthcare services in some police and firefighter’s institutions, including travel-related issues (distance, transit, transportation, and time consumption) and lack of time [26, 27]. This approach enables users to access healthcare services remotely, which may not be available in person within their local areas. Previous meta-analyses have shown that self-managed m-health-based programs may effectively reduce pain and disability in patients with CLBP [28, 29]. However, the effectiveness of exercise-based telerehabilitation strategies on biopsychosocial outcomes in police officers and firefighters with CLBP is not entirely established. Previous systematic review of non-conservative interventions in tactical populations (i.e., police, firefighters, and military personnel) showed that interventions using telerehabilitation approach in this population are scanty [30].

Therefore, this clinical trial will test the effectiveness of an m-health-based self-managed program based on core strengthening exercises plus health education, compared to an m-health education only, on physical and perceptual outcomes. Considering that several studies demonstrate the effectiveness of health education in the clinical outcomes of patients with CLBP, we choose for an active comparator group intending to reach the principle of equipoise. We hypothesize that the effects of an m-health self-managed program based on core strengthening exercises plus health education will be superior on co-primary and secondary outcomes, compared to education health program.

## Methods

### Protocol elaboration and registration

This study protocol follows the recommendations of the SPIRIT (Standard Protocol Items: Recommendations for Interventional Trials) 2013 Statement [31] (see checklist in Additional file 1). The SAFEBACK study is a randomized controlled trial registered on Clinical Trials (NCT05481996) on August 1, 2022, before the first participant enrolment.

### Study design

This study is a prospectively registered, parallel, two-armed, assessor-blinded, superiority randomized controlled trial. Three assessment points were performed (baseline, 8 weeks post-intervention, and 16 weeks follow-up) with probability sampling with randomization in an allocation ratio 1:1. The planned flow diagram of this trial is presented in Fig. 1.

**Fig. 1 Fig1:**
[figure not shown]
Study design

### Study setting and eligibility criteria

This trial was conducted until August 2023 at the *Universidade Federal de Pelotas*, Pelotas, Brazil. The participants were recruited from the Rio Grande do Sul State (Brazil) public safety organizations through advertising in social media, local newspapers, and through professional e-mail of public security organizations involved in the study. Police officers and firefighters were defined as those that belong to the following public security organizations: Federal Police, Federal Highway Police, Civil Police, Military Police, and Military Firefighters. They shared exposure to a range of physical, behavioral, and mental factors known to be associated with LBP experience [13–15]. The recruitment period occurred from October 2022 to May 2023. During recruitment, we determined study eligibility based on inclusion and exclusion criteria defined as follows:

Inclusion criteria:Aged between 18 and 60 yearsCLBP (defined as pain lasting more than 12 weeks);CLBP of at least three points in a 0 to 10 Pain Numerical Rating Scale (NRS) [32];Having a smartphone with internet access and an e-mail account;Police officer (federal, federal highway, civil or military) or military firefighter working in the State of Rio Grande do Sul.

CLBP was defined as pain or discomfort between the 12th ribs and the lower gluteal folds, with or without symptoms referred to the lower limbs, lasting more than 12 weeks (chronicity), not attributed to a specific diagnosis [33].

Exclusion criteria:Neurological symptoms (nerve root compromise or sensation deficits);Spinal severe diseases (e.g., fracture, tumor, inflammatory, autoimmune, and infectious diseases);Severe cardiovascular and metabolic diseases (e.g., coronary heart disease, cardiac insufficiency, decompensated diabetes);Recent spine surgery (over the last 12 months) or scheduled to undergo surgery in the next 6 months;Pregnancy;History of physical therapy treatment for LBP or physical exercise (strength training for core muscles, Pilates, yoga) current or within the last 3 months;Retired;Having any contraindications to exercise.

We pre-screened physical activity participation at baseline using the Physical Activity Readiness Questionnaire (PAR-Q) Portuguese version [34]. The PAR-Q is a physical activity readiness questionnaire consisting of seven closed questions (yes or no). If a “YES” answer was given, the individual was advised to seek medical referral for engaging in physical activity, following the PAR-Q protocol.

### Data collection and management procedures

#### Pre-intervention assessment

After initial contact with researchers, volunteers were scheduled an interview (through a video call) with one of the assessors where the eligibility criteria for participation in the study was checked. Eligible participants received the online consent form via email (see Additional file 2). After online signature, they completed a standardized questionnaire regarding sociodemographic, anthropometric, nutritional, occupational, behavioral, LBP history, and medication use. A second video call was pre-scheduled in the eligibility assessment for data collection related to the self-reported outcomes. Afterward, a face-to-face assessment of the neuromuscular outcomes was conducted. Weight, height, and waist, hip, and abdominal circumferences were recorded in the baseline face to face assessment. Blinded assessors performed all data collection related to the co-primary and secondary outcomes at all time points. All outcomes were assessed 8 weeks after the intervention, while only the online self-reported outcomes were collected at 16 weeks.

The baseline, 8-week, and 16-week online assessments was conducted via video call using a personalized link on the Google Meet platform, and the self-reported data were assessed using the Google Forms platform. All data entries collected by the questionnaire were converted and coded to an Excel spreadsheet (Microsoft Corporation, Redmond, Washington) and double-checked before analysis. The time scheme for study conduction is presented in Fig. 2.

**Fig. 2 Fig2:**
[figure not shown]
Time scheme for study conduction

### Outcome measures

The co-primary outcomes will be pain intensity and disability at 8 weeks (post-treatment). Pain intensity was measured using the 11-point Pain NRS, a numerical scale where 0 indicates no pain and 10 indicates maximum pain intensity, presenting good levels of test–retest reliability intraclass correlation coefficient (ICC = 0.94) [35]. Disability will be measured using the 24-item Roland Morris Disability Questionnaire [36], a questionnaire that assesses normal activities of daily living, where a higher score indicates a higher level of disability and having excellent test–retest reliability (ICC = 0.94) [37].

The secondary outcomes will be as follows:Pain intensity at 16 weeks follow-up;Disability at 16 weeks follow-up;Health-related quality of life at all time points: measured with the WHOQOL-Pain [34], a self-reported questionnaire with 16 questions and classification of 4 facets related to the experience of chronic physical pain. Higher scores reflect better quality of life;Self-efficacy at all time points: measured with the Chronic Pain Self-Efficacy Scale [38], a questionnaire with 22 questions classified into three domains and have internal consistency values ranging from satisfactory to excellent, both for the domains (*α* Cronbach = 0.76–0.92) and for the total scale (*α* Cronbach = 0.94) [39]. Each domain score ranges from 10 to 100. Higher scores reflect a greater sense of self-efficacy;Depression, Anxiety, and Stress at all time points: measured by the Depression Anxiety Stress Scale [40], a self-reported scale with 21 questions, 7 for depression, 7 for anxiety, and 7 for stress with a construct validity and internal consistency that ranges from strong to excellent (*r* = 0.74–0.86; *α* Cronbach = 0.86 0.0.92, respectively) [40]. Each question ranges from 0 to 3 according to the patient’s response. Higher scores indicate worst results;Sleep quality at all time points: measured by the Pittsburgh Sleep Quality Index [41], a self-reported scale with 19 questions that assess seven components of sleep and has a high degree of internal consistency (*α* Cronbach = 0.82) [41]. Each question ranges from 0 to 3 according to the patient’s response;Work ability at all time points: measured by a single-item question, “Are you working at a physically less demanding job now because of your back and/or leg pain?” [42, 43];Isometric muscular endurance of the trunk extensor at 8 weeks (post-treatment): measured by the modified Biering-Sorensen test [44]. This test indicates the time the participant can remain with the trunk in a horizontal and straight position. This test has moderate test–retest reliability (ICC = 0.87) among individuals with CLBP [44]. Longer time indicates better isometric resistance scores;Isometric muscular endurance of the trunk flexors at 8 weeks (post-treatment): measured by a test that consists of remaining in isometry as long as possible in a sitting position with 45° hip flexion [45]. The longer the time indicates better isometric resistance scores;Maximum isometric strength of the trunk extensor and flexor muscles at 8 weeks (post-treatment): maximum voluntary isometric contraction (MVIC) was measured by a calibrated load cell (Miotec®, Porto Alegre, Brasil) of 200 kgf. For the MVIC test of the trunk flexors muscles, the participants were positioned in a sitting position on top of the stretcher, with knees extended, legs fixed to the stretcher with two traction straps, hips flexed and resting on the backrest of the stretcher adjusted at 30° the surface of the stretcher, and arms crossed in front of the torso. For the MVIC test of the trunk extensor muscles, the participants were positioned in ventral decubitus, with knees extended and legs fixed to the stretcher with traction straps and elbows flexed with hands superimposed on the head. For both tests, the load cell was attached to an adapted stretcher, aligned perpendicularly to the torso, passing through the stretcher’s aperture. Chains connected the load cell to a traction belt positioned at rib height (xiphoid process). Participants performed three 5-s attempts for each position, with a 2-min interval between each attempt. During the tests, participants were verbally encouraged to apply maximum force as quickly as possible. The cell load values (kgf) were transformed into Newton (N) and multiplied by the distance (m) between the hip joint (greater trochanter of the femur) and the point of attachment of the traction belt to calculate peak torque in N.m;Muscular activation of spine flexor and extensor muscles at 8 weeks (post-treatment): simultaneously with the MVIC collection, the neuromuscular activation of the trunk flexor (rectus abdominis) and extensors (erector spinae—longissimus) muscles was measured using the surface electromyography technique (sEMG). A Miotool device (Miotec®, Porto Alegre, Brazil) was used with 1 cm Ag/AgCl electrodes (Meditrace®, Mansfield, Canada) and an interelectrode distance of 30 mm. The sEMG signal was collected from the right side of the participant’s body. During the assessments, the recommendations of skin preparation, asepsis, and fixation of the SENIAM electrodes were observed [46]. The electrodes’ location on the erector spinae was carried out according to SENIAM guidelines (i.e., two finger widths laterally from the spinal process of L1). In the rectus abdominis muscle, the electrodes were positioned 3 cm laterally to the body midline on the muscle belly between the sternum and the umbilicus [47]. A reference electrode was placed on the participants right clavicle. Maps were made to help reposition the electrodes after the intervention (8 weeks) by marking anatomical points and signs on the skin in transparent plastic.Occupational performance at 8 weeks (post-treatment): measured by a task that simulates a victim rescue. The participant will drag a dummy (weight = 60 kg) away from the start line, around a cone placed at the 13 m mark, and return to the start line. The longer the time indicates worse occupational performance.

Eligible participants were randomly allocated to the intervention or control group with a 1:1 simple allocation using a computer-generated randomization sequence created by a blinded investigator via a random function in Excel software for Windows. After randomization, an independent researcher emailed each participant the login and password to access the specific app version to which they were allocated (intervention or control). Afterward, an assistant researcher inserted them into numbered, sealed, and opaque envelopes.

### Blinding

Due to the intervention’s characteristics, blinding of participants and intervention providers was not possible. The outcome assessors were blinded to the treatment groups. Participants are asked to omit their assigned group and not discuss their interventions during the outcome assessments. In unblinding cases, the principal investigator was notified with the participant ID, date, and reasons for unblinding.

### Interventions

Intervention descriptions followed the TIDieR (Template for the Intervention Description and Replication) checklist recommendations for telehealth interventions used in clinical trials [48].

#### Intervention group: m-health-based pain education and exercise

Patients allocated to the experimental group received a login and password for individual access to the smartphone app (www.mysafebackapp.web.app/). Before the intervention begins, participants received a yoga mat, an elastic band, and a link to a tutorial video showing how to use the app functions. The app content for this group included three components: (1) a physical exercise program of 8 weeks, (2) weekly messages, and (3) an online booklet.

The exercise component (app “training” function) included 8 weeks of training, with two sessions per week (non-consecutive days) of core strengthening exercises. The exercise program was developed by exercise professionals with at least 5 years of clinical experience, specialists in chronic pain treatment, and who used exercise-based treatment. The training periodization followed the progression of pre-established protocols for CLBP treatment reported in the literature (see training periodization in Additional file 3) [49–52]. The exercises performed in each stage are presented in Additional file 4.

The app provided animated Graphics Interchange Format (GIFs), descriptions, and audio of how to perform each exercise. The number of repetitions or time under tension for each exercise were prescribed with a range of target zones (e.g., 10–12 repetitions, 20–30 s). For those who cannot reach these zones, they were asked to indicate (on the app) that they could not perform the complete exercise. Exercise sessions were carried out remotely and self-managed by the participant (i.e., the participants were responsible for carrying out the exercises). The content of the training sessions was made available (visible in the app version) each week of intervention training.

The message component from the app provided 8 messages (one per week), with the contents taken from the online booklet. Messages included information about the benefits of exercise, motivation, and positive messages about coping with pain.

The online booklet contained general information about self-management of chronic pain, including pain education, advice on healthy lifestyle and sleeping habits, and promotion of exercises. The “Contact” function from the app provided participants a direct communication with the researcher to answer questions about the app, its features, and information about possible app errors. In addition, to improve training adherence, the app provided a count and progression bar (%) of the number of completed training days. Adherence was defined as the absolute and relative frequency of the number of sessions performed.

#### Control group: m-health-booklet and pain education

Patients allocated to the control group received a login and password for individual access to the smartphone app designed for the study. The app content for this group included two components: (1) an online booklet and (2) weekly messages. The online booklet contained general information about self-management of CLBP, including pain education, advice on healthy lifestyle and sleeping habits, and promotion of physical activities based on the “Back Book” (see Additional file 5).

The message component provided 8 messages (one per week), with their contents taken from the online booklet. Messages included information about the benefits of exercise, motivation, and positive messages about coping with pain. Before intervention begins, participants received a yoga mat, an elastic band, and a link to a video tutorial on how to use the app. To increase adherence to the intervention, after the study is concluded, the training function available in the app will be offered to the control group participants if the intervention group proved to be more effective than the control group.

### Strategies for trial retention

Participants allocated to both groups received, in week 4, WhatsApp messages to reinforce the use of the app. There are prohibited concomitant interventions including any systematic or supervised physical exercise to strengthen core (e. g., Pilates, Yoga). Any exercise should be reported by the participants and documented for future discussions.

### Statistical methods

#### Sample size calculation

Sample size estimation was performed a priori through G-Power’s statistical software (version 3) [53]. A sample size calculation determined that a minimum of 66 individuals would be required in the present study. Data used included 80% power to detect a between-group difference of 1.5 points in a 0 to 10 Pain NRS [54, 55], with an estimated standard deviation (SD) of 2.0 points [56], and a between-group difference of 4.0 points in a 1 to 24 points RMDQ [57], with an estimated SD of 4.9 points [58] and alpha error (two-tailed) of 5%. The estimated sample size would also allow for a loss to follow-up rate of up to 15% observed in studies involving similar populations (firefighters and military) and forms of intervention provision (i.e., app) [56, 59].

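### The stated 80% power is for pain alone; for superiority on both co-primary outcomes, power at the planned 15% loss is about 67–75%

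*Protocol article*

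**What the plan says.** The Outcome measures section defines two co-primary outcomes at one time point: "The co-primary outcomes will be pain intensity and disability at 8 weeks (post-treatment").

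The Sample size calculation section gives a single power and a single alpha for the two together. For pain it claims "80% power to detect a between-group difference of 1.5 points in a 0 to 10 Pain NRS", "with an estimated standard deviation (SD) of 2.0 points". For disability it assumes "a between-group difference of 4.0 points in a 1 to 24 points RMDQ", "with an estimated SD of 4.9 points". The alpha is given once, as "alpha error (two-tailed) of 5" per cent. The minimum total is 66, said to allow for up to 15% loss. The section gives no joint power and no correlation between the outcomes.

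The hypothesis in the abstract is that the effects "on co-primary and secondary outcomes will be superior", and the Background repeats it. The Data analysis section plans between-group differences with 95% confidence intervals from linear mixed models. It does not say how the two co-primary results combine into one conclusion.

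**The concern.** With two co-primary outcomes, the chance that the trial supports its conclusion depends on how the two results are joined. If both must succeed, the trial can fail on either one, so its power is lower than that of the weaker outcome taken alone. A sample size set by one outcome at 80% then leaves the joint claim below 80%.

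The practical stake is a split result, for example pain significant and disability not. The article does not say whether that counts as superiority. The Control group section and the Harms section also make controls' access to the training function depend on the intervention proving more effective, without naming the outcome that decides this. A reader who takes 80% as the power of the trial would judge a failed joint claim against a 20% risk, when the risk is nearer 25–33%.

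**Working it through.** **Inputs from the Sample size calculation section:** pain 1.5/2.0, so d = 0.75; disability 4.0/4.9, so d = 0.816; two-sided alpha 5%; power 80%; loss 15%; N = 66. Allocation is 1:1 (Study design). **Assumed:** between-outcome correlation from 0 to 0.8, because the article gives none.

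**Step 1: reproduce 66.** By the normal approximation, n per arm = 2(1.960 + 0.842)²/d².
- Pain: 2 × 7.849/0.5625 = 27.9, so 28 per arm and 56 in total; 56/0.85 = 65.9, so 66. This matches the plan.
- Disability: 2 × 7.849/0.6664 = 23.6, so 24 per arm and 48 in total; 48/0.85 = 56.5, so 57.

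Pain alone sets N, and nothing is added for the second outcome.

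**Step 2: power for each outcome at 15% loss.** 66 × 0.85 = 56.1, or 28 per arm.

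| Outcome | Normal approximation | Two-sample t-test |
|---|---|---|
| Pain | 80.1% | 78.7% |
| Disability | 86.3% | 85.1% |

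**Step 3: power for both outcomes, each at two-sided 5%.** At correlation 0 the joint power is the product: 0.787 × 0.851 = 0.670. For other correlations, correlated outcomes were simulated and t-tested (200,000 replicates per row). The normal-approximation column is the bivariate normal probability that both statistics pass 1.960.

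| Correlation (assumed) | 28 per arm, t-test | 28 per arm, normal approx. | 33 per arm (no loss), t-test |
|---|---|---|---|
| 0 | 67% | 69% | 77% |
| 0.3 | 69% | 71% | 78% |
| 0.5 | 71% | 73% | 80% |
| 0.7 | 73% | 75% | 81% |
| 0.8 | 75% | 76% | 82% |

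At 28 per arm every entry is below 80%. With no loss, the joint figure lies on either side of 80%, depending on the correlation.

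**Step 4: error rate.**
- If both outcomes are required, the chance of a false claim is at most 5% with each tested at 5%. No adjustment is needed.
- If either outcome sufficed at an unadjusted 5%, the familywise error at correlation 0 would be 1 − 0.95² = 9.75%. It would be 9.5%, 9.1%, 8.3% and 7.8% at correlations 0.3, 0.5, 0.7 and 0.8, so about 8–10%. That reading would need Holm, an alpha split or a fixed testing order.

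**The case against.** Five points can be made for the plan.

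- **The 80% can be read per outcome.** On that ordinary reading the statement is nearly right: 79–80% for pain and 85–86% for disability. This stands. A reader might infer that 80% power and 5% error can never hold together at this sample size, or that the pair is wrong under any reading. The article does not support that. A fixed order with pain first keeps 5% error with about 79–80% power on pain. Holm keeps 5% with roughly 82–93% power for at least one outcome over the same correlations. Both support a narrower claim than superiority on both outcomes, and neither is stated.
- **A reader might infer a doubled false-positive rate.** The either-outcome rule behind that figure is not in the text. The hypothesis leans towards both, where 5% each is correct.
- **Loss is a ceiling.** The section allows for up to 15%, so 28 per arm is the planned worst case. This stands, and it is why the no-loss range is shown. But the section claims 80% with that loss allowed for.
- **The mixed model uses the baseline measurement.** If baseline is a covariate correlated 0.4 with the 8-week value, the effective size is 28/(1 − 0.4²) = 33.3 per arm, which gives about 80–81% joint power at between-outcome correlations of 0.5–0.7. But a contrast of change from baseline at the same correlation has variance 2(1 − 0.4) = 1.2 times the raw variance, which is a loss. The article does not say which applies, and its sample size does not rely on a gain.
- **A success rule may sit in an analysis plan that is not shown.** This also stands, so the absence of a rule is not by itself the point. The point is the power figure attached to N, which the protocol does fix.

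**Conclusion.** The point holds in a limited form. The calculation for pain is correct and reproduces 66, but the 80% attached to it is not the power of the two-outcome superiority claim. With 28 completers per arm, that power is about 67–75%, a shortfall of 5 to 13 percentage points. With no loss it is 77–82%.

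These figures rest on the article's own effect sizes and standard deviations, unadjusted two-sample t-tests, the full 15% loss, and a between-outcome correlation of 0 to 0.8 that is assumed. On the both-outcomes reading, control of the type I error is sound. The 8–10% familywise error arises only under an unadjusted either-outcome rule, which the article does not state.

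This should be fixed. It affects how a split or negative result is interpreted and does not invalidate the design.

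**What to change.** 1. In the Data analysis section, or in a dated analysis plan, state that superiority is concluded only if both 8-week contrasts have two-sided p<0.05, with no alpha split, and that a split result does not meet the primary objective. If the sponsor instead intends one outcome to suffice, name Holm, an alpha split or a fixed testing order.
2. Restate the sample size paragraph: at 15% loss, power is about 79% for pain and 85% for disability, and about 70% for both, with the assumed correlation given.
3. Set the rule before the data are analysed or unblinded. The article reports that recruitment closed in May 2023 and that the trial ran until August 2023. If the rule is set after the data have been seen, say so and report both outcomes with that caveat.

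The cost is a few sentences, recorded through the amendment route described under Trial status, and a less favourable stated power. No participants are added. For context, 80% joint power at 15% loss would have needed about 73–80 randomised by the normal approximation (31–34 per arm evaluable, over correlations 0.8 down to 0), but recruitment has ended.
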